### Data collection

For the duration of the study, migrant patients will be assigned to a personal clinician as they will be required to complete questionnaires about each other. Before the start of treatment, clinicians will be informed of the randomization group to which the migrant patient has been assigned. Participating confidants will have one consultation with the personal clinician of the patient that they represent, according to the patient’s randomization status.

The principal investigator will receive notification regarding the date of the initial treatment session to schedule an appointment for the migrant patient to take the first-stage survey on perceived empathy, either face-to-face or online. The respective questionnaires must be completed within one week of the first session, and interpreters will be employed as necessary. The patient proceeds with subsequent treatment following the treatment plan. The procedure for participating confidants will be identical, and their involvement will cease upon finishing the perceived empathy questionnaire (see **Figure 1**).

In the intervention group, treatment sessions will proceed using CFI questions. The control group will receive standard care in which CFI questions are avoided. After each initial treatment session, clinicians will complete a brief online questionnaire to evaluate their fidelity to the CFI. Fidelity is expected for migrant patients who were randomized in the intervention group, and infidelity to the CFI is expected in the control group. In addition, the clinicians will be asked to respond to empathy-related questions.

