The principal investigator will receive notice of the migrant patient’s fifth treatment session appointment with their personal clinician to schedule the second-stage questionnaire completion. The patients will have an in-person or online appointment where they will answer the same questions about perceived empathy, in addition to supplementary questions about the therapeutic working alliance. The questionnaires need to be completed within one week of the fifth session. After the completion of these questionnaires, the patient’s participation concludes. Subsequently, clinicians will conduct an online questionnaire after every fifth treatment session. This questionnaire includes the same fidelity check and empathy questions as offered after the first treatment session and additional questions regarding the therapeutic working alliance. Clinicians will continue treating other study participants and are required to reiterate the aforementioned protocol for each participating patient under their care. Their participation in this study will end after completing the questionnaires of their final migrant patient.

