### Benefits and consequences of participation

In line with the aim of this study, patients in the intervention group may benefit from the experience of a stronger therapeutic working alliance and a higher level of perceived cultural empathy. The risk of negative consequences of participation is estimated to be as low, if not non-existent since patients in the control group also receive the current standard of treatment and care. The additional burden of participation for patients is to complete questionnaires before and after the first and after the fifth treatment session, which will take some extra time.

Participating clinicians benefit from free CFI training that can enhance their clinical competencies and future therapeutic working alliances with patients and their confidants. The additional obligation for participating clinicians entails investing additional time in consultations with confidants and completing the online surveys for each of their participating patients before and during the study, which adds extra time to their workloads.

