#### Clinicians’ level of cultural empathy

The Scale of Ethnocultural Empathy (SEE) will be used to measure the clinician’s level of cultural empathy in the context of the previous treatment session(s) (30). The 31 items are scored on a 6-point Likert scale. For this study, three researchers independently translated the English SEE into Dutch. Differences in the translations were discussed until a consensus was reached. The scale measures four empathy factors: empathic feeling and expression (EFE), ethnocultural empathy awareness (EA), acceptance of cultural differences (AC), and empathic perspective-taking (EP). It takes approximately 10 minutes for clinicians to complete the questionnaire.

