### Data analysis

Analyses will be performed using intention-to-treat principles. Missing data will be imputed using multiple imputation if assumptions are not violated. Non-parametric equivalents (Mann-Whitney U-tests) will be used when appropriate. All analyses will be performed taking into account the structure of the dataset (individuals within the four institutions: migrant patients, confidants, and clinicians). Data will be coded according to randomization.

Data analysis will be performed using SPSS-28. SEE, BLRI, and WAI scores will be calculated according to the instrument’s guidelines. Mean WAI scores between the intervention and control groups will be compared using t-test analyses. Linear regression analysis will be used to examine the main effect of CFI use on therapeutic working alliance and to test whether perceived empathy (BLRI and SEE) moderates (changes in strength and direction) the relationship between the use of the CFI and therapeutic working alliance when this relationship occurs. In addition, it will be tested whether perceived empathy (BLRI and SEE) mediates (explains) the relationship between the use of the CFI and working alliance within the framework of Baron & Kenny (33). **Figure 2** shows the to be examined moderating or mediating effect of perceived empathy in the analyses. To test for differences in the three analyses above, age, sex, generational status, country of origin, educational level, occupation, profession, religion, and religiosity of the migrant patients will be included as covariates or grouping variables in the analyses. In addition, the influence of gender differences among clinicians, work experience, and prior experience with the CFI will be explored.

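### Empathy is tested as a moderator of the CFI effect, but both empathy scales are first measured after CFI exposure, so the interaction cannot be read as effect modification

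*Protocol article*

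**What the plan says.** The Data analysis section compares mean WAI between arms by t-test. It then uses linear regression to test whether perceived empathy, measured by BLRI and SEE, "moderates (changes in strength and direction) the relationship between the use of the CFI and therapeutic working alliance when this relationship occurs". The next sentence gives the same scores a second role: "it will be tested whether perceived empathy (BLRI and SEE) mediates (explains) the relationship between the use of the CFI and working alliance".

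The measurement schedule is in Data collection and Table 1. For the patient's BLRI: "The respective questionnaires must be completed within one week of the first session". For the clinician, the same section says "After each initial treatment session, clinicians will complete a brief online questionnaire to evaluate their fidelity to the CFI", with the empathy items asked at that point. The form after the fifth session repeats "the same fidelity check and empathy questions as offered after the first treatment session". The section on clinicians' cultural empathy ties the SEE to sessions already held. The only items that Table 1 places at enrolment are consent and demographics.

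Under Benefits and consequences of participation, intervention patients may gain "a stronger therapeutic working alliance and a higher level of perceived cultural empathy". The Introduction, like Data analysis, defines moderation as covering direction as well as strength.

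**The concern.** A moderator answers the question: for which patients, or with which clinicians, does the CFI work better? For that, the variable must be fixed before the treatment can act on it. A score that the CFI may itself have changed does not mean the same thing in the two arms. Comparing CFI with control patients at equal post-session empathy is then no longer a randomised comparison. The interaction can be non-zero without any effect modification, and the arm coefficient in that model departs from the total CFI effect.

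The closing condition raises a second problem. If moderation is examined only once a main effect has been found, a CFI effect that helps in some patients and harms in others could cancel in the mean and never be examined.

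Much rests on this analysis: the stated hypothesis is a positive effect moderated by empathy, and the abstract promises an answer on moderation.

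**Working it through.** **Step 1. Order of events.**

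| Time | Patient | Clinician |
|---|---|---|
| Before first session | consent, demographics; randomised | consent, demographics, CFI training; told the allocation |
| First session | CFI questions used (intervention) or avoided (control) | same |
| After first session | BLRI | fidelity check, SEE |
| After fifth session | BLRI, WAI | fidelity check, SEE, WAI |

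No BLRI or SEE precedes the CFI. The Benefits section speaks of questionnaires before and after the first session. Table 1 and the recruitment section show that the earlier ones are consent and demographics.

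**Step 2. The plan's sample size.** Take 0.39 as a standardised difference, with alpha 0.05 and power 0.80 (Sample size section). One-sided, n per arm = 2(1.645 + 0.842)²/0.39² = 81.3, rounded up to 82, so N = 164, as stated. Two-sided, n per arm = 2(1.960 + 0.842)²/0.39² = 103.2, rounded up to 104, so N = 208, close to the 209 given for the regression. The sidedness is not stated. I use N = 164 below.

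**Step 3. False interactions with a post-CFI score.** All effect sizes here are assumptions. In SD units, an unmeasured trait U loads λ on pre-CFI empathy and on WAI, each with variance 1. The CFI adds a constant 0.5 to WAI, so there is no moderation. In the CFI arm, empathy shifts by 0.5 with between-patient SD s.

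- Slope of WAI on empathy: λ² in control, λ²/(1 + s²) with CFI.
- Apparent interaction: λ²/(1 + s²) − λ².
- For λ = 0.7, s = 0.8: 0.49/1.64 − 0.49 = −0.191.
- Standard error: √[(1 − 0.49²)/82 + (1 − 0.49²/1.64)/(82 × 1.64)] = √(0.00927 + 0.00635) = 0.125.
- Ratio −1.53, so the rejection probability is Φ(1.53 − 1.96) ≈ 0.33.

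Simulated rejection rates (3000 trials per case, two-sided 5%; a range is given where the case was run more than once):

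| λ | s = 0 | s = 0.3 | s = 0.5 | s = 0.8 |
|---|---|---|---|---|
| 0.7 | 4.9–5.4% | 7% | 10.5–11.9% | 32–33% |
| 0.5 | – | – | 7% | 12% |
| 0.4 | – | – | 5% | 7% |

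With λ = 0.7, using the pre-CFI score on the same data gives 4.4–5.4%. In a different model, the CFI changes how strongly empathy reflects the trait and the CFI effect is 0.39. There the post-CFI score gives 15.0% and a pre-CFI score 4.5% (4000 trials, N = 164).

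**Step 4. CFI coefficient in the same model.** With λ = 0.7 and s = 0 it is 0.5 − 0.49 × 0.5 = 0.255, against a total effect of 0.50. In simulation it is 0.25 to 0.30 for s from 0 to 0.8. So it misses the total effect even where the interaction test keeps its 5% level.

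**Step 5. The condition, if it is a 5% significance gate.** If opposing effects cancel exactly, the main effect is zero and the gate opens in about 5% of trials by construction. With a pre-randomisation moderator and an interaction of 0.5 per SD, the interaction is detected in 87.7% of trials without the gate and 4.8% with it (N = 164). With 0.45 per SD the figures are about 80% and 4%. If the planned 0.39 is true, a two-sided gate at N = 164 opens in 69.9% of trials, so about 30% would skip the moderation test.

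**The case against.** Several points on the other side stand.

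- **The main comparison.** A reader might infer that the trial's main result is biased. It is not: the WAI t-test does not adjust for empathy. The coefficient in Step 4 arises only in models that contain empathy.
- **Size of the inflation.** If the CFI simply raises everyone's empathy by the same amount, the interaction test holds its level. Inflation needs a shift that varies between patients and a common cause of both scales, and the documents give no figure for either. It would be wrong to attach one inflated error rate to this trial.
- **The gate.** A reader might take the condition as a formal significance rule. The text names no test or threshold, and the Introduction poses the moderation question without conditions. Sequential testing is the natural reading, but not the only one.
- **A near-zero mean effect.** A reader might infer that the protocol foresees benefit and harm cancelling out. It does not. The Introduction says alliances generally benefit, notes that harm is possible, and hypothesises a positive effect. The cancelling case is an illustration, and its 5% follows from setting the mean to zero.
- **Status of the analysis.** The Study context section calls this part an exploration, although the objective and the hypothesis both include it.

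One might add that assigning time points to roles can be left to an analysis plan. That does not help here: no pre-CFI empathy score is scheduled, and no later plan can create one.

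**Conclusion.** The timing point holds on the text alone. The planned interactions with BLRI and SEE use post-randomisation scores that the protocol expects the CFI to change, and that it also treats as mediators. They cannot be read as effect modification, and the CFI coefficient beside them is not the total effect. The false-interaction rate runs from about 5% (equal shift in all patients) to about 5–33% (shift SD 0.3–0.8, trait loading 0.4–0.7, N = 164). This range illustrates the mechanism and does not estimate what will happen in this trial.

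The condition on the moderation test is a second, weaker point. It is ambiguous, and on its likely reading it could suppress the change of direction that the protocol's own definition of moderation includes.

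Severity: should-fix. The point concerns the secondary moderation question, and the main comparison of WAI stands.

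**What to change.** 1. Add the SEE, worded as a general clinician trait, to the online consent and demographic form that clinicians already complete. Have it completed before the clinician's first randomised patient, and state whether this is before or after CFI training. Either is before randomisation, but the score may differ.
2. Make arm × baseline SEE the moderation test, allowing for clustering of patients by clinician.
3. Keep the post-session BLRI and SEE for the mediation analysis only, and do not report them as effect modifiers.
4. Delete the closing condition in "the relationship between the use of the CFI and therapeutic working alliance when this relationship occurs" and report the interaction with its 95% CI whatever the main effect.
5. State that moderation by patient-perceived empathy (BLRI) cannot be answered with this schedule.

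Cost: about 10 minutes per clinician, the time the protocol gives for the SEE, plus changes of wording. Precision will depend on the number of clinicians, which the article does not give, and the moderation question narrows to a clinician trait. If a baseline SEE can no longer be collected, items 3 to 5 still apply to the reporting, and the moderation question should be declared unanswered.

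### The mediation analysis relies on the Baron & Kenny steps, which lose power when the total effect is small, and the plan does not say which empathy measurement is the mediator

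*Protocol article*

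**What the plan says.** The Data analysis section of the protocol article compares mean WAI scores by t-test, tests moderation by linear regression, and then adds a test of whether empathy, measured by BLRI and SEE, "mediates (explains) the relationship between the use of the CFI and working alliance within the framework of Baron & Kenny". It lists no steps and names no test of the indirect effect.

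The measurement schedule is in the Data collection section and Table 1:

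- **Patient, session 1:** the patient is scheduled "to take the first-stage survey on perceived empathy, either face-to-face or online". No WAI is taken.
- **Patient, session 5:** at one appointment, patients "answer the same questions about perceived empathy, in addition to supplementary questions about the therapeutic working alliance". This is the only patient WAI.
- **Clinician, session 5:** the online questionnaire holds the "same fidelity check and empathy questions as offered after the first treatment session and additional questions regarding the therapeutic working alliance". The session-5 SEE and the clinician WAI are therefore also completed together.

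The Data analysis section does not say which occasion supplies the mediator. It places BLRI and SEE together under perceived empathy, whereas the Measures section defines SEE as the clinician's own level of cultural empathy and keeps perceived empathy for the BLRI.

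**The concern.** There are two separate problems.

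**Method.** In the classical causal steps, mediation is declared only if the total effect (CFI on WAI), path a (CFI on empathy) and path b (empathy on WAI, given arm) are each significant and the direct effect is smaller than the total effect. The power to detect mediation then cannot exceed the power for the total effect, however strong the two paths are. The product a x b is neither tested nor given an interval.

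**Mediator occasion.** A session-5 BLRI does not precede the WAI and shares rater and sitting with it. Anything that moves both answers, such as mood or general satisfaction, enters path b as if empathy had caused alliance. Because the occasion is open, an ordered mediator and a same-sitting mediator are both allowed.

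At stake is the explanatory part of the trial. Real mediation could be missed if the CFI effect is modest, or a same-sitting correlation could be reported as mediation. The Strengths and limitations section itself expects possible contamination of the control group and underestimated results, so a total effect below the planning value is a realistic case.

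**Working it through.** **The plan's own figure.** The Sample size section gives no power for mediation. Its 164 patients (82 per arm) reproduce as a one-sided 5% t-test with a standardised difference of 0.39 (power 80.0%). Two-sided, 164 gives 69.9%. The text calls 0.39 half an SD. If it is a raw half SD, the standardised effect is 0.50, so that reading is carried along below.

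**Inputs.** From the plan: N = 164, 1:1, alpha 0.05 (two-sided here; the plan does not state sidedness). Assumed, because the documents give no values: a = 0.5, b = 0.4, unit residual SDs, residual correlation 0.15 or 0.30, no dropout, no clustering.

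**1. Power when mediation is real**

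The within-arm WAI SD is sqrt(1 + 0.4²) = 1.077. For a standardised total effect d, z = d x sqrt(82/2) = 6.403d, and power is about Phi(z - 1.96).

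- No direct effect: total = 0.5 x 0.4 = 0.20, d = 0.20/1.077 = 0.186, z = 1.19, power for the total effect 22%.
- Direct effect 0.19: total = 0.39, d = 0.39/1.077 = 0.362, z = 2.32, power 64%.
- Direct effect 0.22: total = 0.42, d = 0.39, z = 2.50, power 70%.

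Each is a ceiling for the causal steps. A direct test needs only a and b. For a, z = 0.5 x 6.403 = 3.20, power 89%. For b, z = 0.4 x sqrt(164) = 5.12, power above 99%. The product is about 89% in all three cases.

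Simulation at N = 164 agrees (repeat runs differ by a point or two):

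| Total effect | Causal steps | Direct test | Share of power kept |
|---|---|---|---|
| 0.19 SD | 22% | 89% | 22/89 = 25% |
| 0.36 SD | 59% | 89% | 59/89 = 66% |
| 0.39 SD | 65% | 89% | 65/89 = 73% |

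With other assumed inputs (b = 0.39 or 0.59; half or all of the effect mediated), the steps keep about 70-86% of the direct test's power at d = 0.39 and 88-95% at d = 0.50.

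**2. False mediation with a session-5 mediator**

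Set the true b to 0, the total effect to 0.39 SD and a to 0.5, and let the BLRI and WAI residuals correlate at r. Path b then estimates r instead of 0, with z = r x sqrt(164)/sqrt(1 - r²).

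- r = 0.15: z = 1.94, b significant in 49%. Direct test about 0.49 x 0.89 = 44%. Causal steps about 0.44 x 0.70 = 31%.
- r = 0.30: z = 4.03, b significant in 98%. Direct test about 0.98 x 0.89 = 87%. Causal steps about 0.87 x 0.70 = 61%.

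Simulated values:

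| r | Causal steps | Direct test |
|---|---|---|
| 0 | about 2% | about 4% |
| 0.15 | 30% | 42% |
| 0.30 | 62% | 86% |

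If the CFI does not affect empathy (a = 0), r = 0.30 gives only about 2% and 5%. The error therefore needs both the shared correlation and a CFI effect on empathy.

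**The case against.** The strongest case on the other side has four parts.

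- **The gate is inferred.** The words "the relationship between the use of the CFI and therapeutic working alliance when this relationship occurs" qualify moderation, not mediation, and working within a framework does not rule out an added test of the indirect effect. This stands in part. The power figures apply to the classical steps. If the unseen analysis plan already tests a x b with an interval whatever the total effect shows, the first problem falls away. Still, Baron & Kenny is the method this article states, so it is not merely a detail left out.
- **Same-sitting measurement is not the fixed plan.** This stands. Session-1 BLRI and SEE precede every WAI, so the design already contains an ordered mediator. The fault is only that the occasion is open, and the full plan may settle it.
- **Baron & Kenny does not create the false mediation.** This stands. A reader might infer from the 30-62% that the causal steps are to blame, but a direct test is misled more often (42-86%). The source is shared rater and sitting.
- **Mediation is secondary.** This stands. The Introduction makes the CFI effect on alliance the central question, adds mediation to it, and words its hypothesis as moderation.

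A reader might also infer that BLRI and SEE are pooled. The documents do not say so: each is scored by its own guidelines, and the shared label is loose wording. Centre structure and patient covariates are already provided for in the Data analysis section.

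**Conclusion.** The point holds in a limited form. A direct estimate of the indirect effect is better than the stated method. At N = 164, with a = 0.5 and b = 0.4, it detects mediation in 89% of trials, against about 59-65% for the causal steps near a total effect of 0.39 SD and 22% near 0.2 SD. It would be tempting to say that the steps lose most of the power. That holds only when the total effect is well below the planning value; at 0.39 SD they keep roughly two-thirds or more, and at 0.50 SD most of it.

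Separately, the mediator occasion should be fixed. If session-5 BLRI is used and the CFI raises both scores, residual correlations of 0.15-0.30 produce false mediation often enough to make a positive finding uninterpretable under either test. The paths and the correlations are assumptions, so the sizes are illustrative, but the direction does not depend on the exact values. The primary comparison of WAI scores is untouched.

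**What to change.** For this secondary analysis, state that:

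1. the session-1 BLRI is the main mediator and the session-5 WAI-12 is the outcome;
2. the indirect effect a x b is estimated with a bootstrap or Monte Carlo 95% CI, whatever the significance of the total effect, with the centre structure and patient covariates already planned;
3. a sensitivity analysis for unmeasured mediator-outcome confounding is reported, because the patient still rates both scales and session 1 removes only the shared sitting;
4. session-5 BLRI and SEE are separate exploratory mediators, with SEE labelled as clinician self-report.

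The cost is analysis wording and a little programming. Every measure is already in Table 1, so no visit, instrument or patient is added. The drawback is that session-1 BLRI misses any change in empathy between sessions 1 and 5; the exploratory session-5 analysis covers that, subject to the bias shown above.
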